### Sample size

For the existing Study 1 the sample size required was previously presented in the published research protocol (1056 mothers: 352 in each of the 3 arms of the study) [21]. A total of 1155 mothers were recruited into the trial exceeding the required sample size by 100 mothers. We originally estimated that a total sample size of 792 (264 per arm × 3) was needed at 2 years to have sufficient power to detect a difference in child BMI of 0.38 kg/m^2^.

For Study 2, we will need a total sample size of 506 (253 per arm × 2) by the end of the study (at 3 years of age). This would allow us to detect a difference of 0.40 kg/m^2^ in mean BMI (SD = 1.60 based on Healthy Beginnings Trial) at the 2-sided 5% significance level with 80% power. This effect size is achievable based on the findings from a 6-month intervention study in the US that detected a decrease in BMI of 0.40 kg/m^2^ with children aged 2–5 years [22]. Allowing for a conservative 15% loss to follow-up between 2 and 3 years, we will need around 600 participants at 2 years of age. This sample size will also give enough power to detect differences in other main outcomes (e.g., a difference of 0.3 in the mean number of daily serves of fruit or vegetables).

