### Retention strategies

We have developed a set of effective cohort retention strategies through the existing CHAT trial [21]. For example, we will send a thank-you card and birthday card for all participating family and children. After hours telephone support calls will be available for mothers who have been back to work in the intervention group.

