### Primary outcomes

The primary outcome is child’s BMI (weight/length^2^; kg/m^2^) or BMI z-score at 3 years of age as used in the previous Healthy Beginnings Trial [13, 15]. Child’s height and weight (and hence BMI, or BMI z-score) will be measured according to the measurement protocol (Additional file 1) in the home by RAs blinded to treatment allocation. Two measures of height will be taken to the nearest 0.1 cm using a portable stadiometer. Measurements of weight (to the nearest 0.1 kg) will be taken using digital scales with the child wearing light clothing and no shoes.

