### Data analysis

CONSORT guidelines for reporting randomised controlled trials will be followed to analyse and report the results. Intention-to-treat principles will be adopted to analyse all outcomes. The primary analysis for Study 2 will be adjusted for the stratification by Study 1 treatment group, as per CONSORT guidelines. For continuous variables, such as BMI, or BMI z-score, means will be compared using linear regression. For binary categorical variables, logistic regression model will be used. Secondary analyses will additionally adjust for exact age, and also will use mixed model and multiple imputation to assess the effect of loss to follow-up as used in the previous Healthy Beginnings Trial [13]. Mean differences of BMI or BMI z-score between the intervention and control groups and adjusted odds ratio (AOR) with 95% confidence interval (CI) will be reported.

### Issue of ‘contamination’ and ‘carry-over effect’ from study 1 to study 2

To assess the level of contamination in the control group and also to test whether the intervention group is receiving additional information, we will ask mothers in both groups to report their sources of information on healthy child feeding and active play. Study 1 intervention will be included in the multivariable regression models to adjust for its effect. In our previous study we demonstrated that, without further intervention, the early intervention effects diminish over time [15], so any carry-over effect from Study 1 to Study 2 should be small. Even if there is a carry-over effect, it will be balanced between the intervention and control groups by the stratified randomisation.

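### The primary regression implicitly uses only children measured at 36 months and omits 24-month BMI; the planned methods for loss to follow-up are only secondary

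*Protocol article*

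**What the plan says.** All of the analysis text is in the protocol article, under Data analysis.

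- General principle: "Intention-to-treat principles will be adopted to analyse all outcomes".
- Primary adjustment: "The primary analysis for Study 2 will be adjusted for the stratification by Study 1 treatment group". No other covariate is named for the primary analysis.
- Primary model: "For continuous variables, such as BMI, or BMI z-score, means will be compared using linear regression".
- Loss to follow-up: the secondary analyses add exact age as a covariate, and "also will use mixed model and multiple imputation to assess the effect of loss to follow-up".

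Under Primary outcomes, the endpoint is tied to one time point: "The primary outcome is child’s BMI (weight/length^2^; kg/m^2^) or BMI z-score at 3 years of age". Under Sample size, the required 506 dyads are counted at 3 years, and the number needed at 2 years is then raised: "Allowing for a conservative 15% loss to follow-up between 2 and 3 years". Under Randomisation, allocation follows the 24-month survey and measurement, so every randomised child should have a 24-month BMI.

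The protocol does not say in words which children enter the primary regression.

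**The concern.** A regression of a single 36-month outcome cannot use a child who lacks that outcome unless the value is imputed, and imputation is named only among the secondary analyses. So the plan recognises loss to follow-up as a problem and names two tools for it, but takes its headline result from the model that uses neither. That model also leaves out 24-month BMI, which is likely to be the strongest predictor of 36-month BMI and a plausible correlate of loss.

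Contact differs by arm, so retention could too. The intervention arm gets three calls, text messages with two-way replies and, under Retention strategies, "After hours telephone support calls will be available for mothers who have been back to work in the intervention group". The control arm gets usual care and two booklets. If the children lost differ in BMI from those retained, and this happens at a different rate or in a different pattern in the two arms, the primary contrast shifts. At stake is the accuracy of the main estimate against a modest target of 0.40 kg/m², together with precision given up by not using a baseline value already collected.

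**Working it through.** **1. The plan's own figures.** Inputs from Sample size: difference 0.40, SD 1.60, two-sided 5%, power 80%. The standardised difference is 0.40/1.60 = 0.25. The two-sample t-test calculation gives 252.13, so 253 per arm and 506 in total, as stated. Allowing for 15% loss, 506/0.85 = 595.3, so 596, which agrees with the stated figure of around 600. Power is therefore counted in children measured at 3 years, which fits the reading that the primary analysis uses observed outcomes.

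**2. How many are left out.** At 15% loss, 0.15 × 600 = 90 randomised dyads, or 0.15 × 750 = about 113 if the estimated 750 are enrolled.

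**3. Simple form of the bias.** For one arm, let m be the fraction missing and s the mean BMI of missing children minus that of measured children. The measured-only mean is then too low by m × s, and the bias in the contrast is the difference between the two arms' values of m × s. With m = 0.15 and s = 0.8 in one arm and no selective loss in the other, it is 0.15 × 0.8 = 0.12. With s = 0.8 in both arms and loss of 10% v 20%, it is (0.20 − 0.10) × 0.8 = 0.08. With equal m and s in both arms it is 0.

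**4. Model-based form.** Assumed, because the protocol gives none of these: correlation r = 0.7 between 24- and 36-month BMI; probability of loss following a logistic model in 24-month BMI, with odds ratio 1.5 or 2.2 per SD; no true effect; 300 per arm. The SD of 1.6 is the protocol's. The bias of the regression without 24-month BMI, in kg/m², is:

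| Loss pattern | OR 1.5 | OR 2.2 |
|---|---|---|
| Same mechanism, 15% in each arm | 0 | 0 |
| Same mechanism, 12% v 18% | 0.03 | 0.05 |
| Same mechanism, 10% v 20% | 0.04 | 0.08 |
| 15% in each arm, BMI-related in one arm only | 0.07 | 0.12 |

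For the last row at OR 2.2, r = 0.5 gives 0.09 and r = 0.8 gives 0.14. At OR 1.5 the corresponding values are 0.05 and 0.08.

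Adding 24-month BMI to the model brought the simulated bias to within about 0.005 of zero in every row.

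**5. Precision.** With 255 measured per arm, the standard error without baseline is 1.6 × √(2/255) = 0.142. Conditioning on 24-month BMI multiplies it by √(1 − 0.7²) = 0.714, giving 0.101. The simulated empirical SDs agree: about 0.14 and 0.10.

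**The case against.** **Intention-to-treat.** A reader might infer that the plan contradicts its own intention-to-treat promise. It does not. The text speaks of principles, and analysing observed outcomes by allocated arm, with pre-specified multiple imputation and a mixed model in support, is a common way to apply them.

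**Need for loss unrelated to BMI.** A reader might also infer that the primary model is unbiased only if loss is unrelated to BMI within arm and stratum. That condition is sufficient but not necessary. If heavier children are lost in the same way and at the same rate in both arms, both means shift equally and the contrast is unaffected, as the first row of the table shows.

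**Size.** The upper figure of about 0.12 needs BMI-related loss in one arm and purely random loss in the other. Nothing in the protocol points to that pattern. The contact argument points rather to unequal rates, for which the bias is 0.03 to 0.08.

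**Retention.** The protocol also works on control-arm retention: the control booklets are meant to keep mothers engaged and limit attrition, and cards go to all families. More contact could also be a burden, so the direction of any difference is unknown.

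**Detail left to another document.** That only measured children enter the regression is an inference, and a statistical analysis plan that is not shown may define the analysis set. All of these objections stand. What remains is the ranking, which the protocol does fix: the model without baseline BMI is primary, and the methods for loss are secondary.

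**Conclusion.** The point holds as a worthwhile improvement, not as an error or a contradiction. As written, the primary estimate by implication rests on children measured at 36 months and does not use 24-month BMI. Under the assumptions shown, the exposure runs from 0 to about 0.12 kg/m², or 0 to 30% of the 0.40 target (0.12/0.40). Where the loss mechanism is common to both arms and only the rates differ, it is about 0.03 to 0.08 (roughly 7% to 20%). These figures depend on assumed values for the correlation and for the link between BMI and loss. The protocol shows neither that loss will differ by arm nor in which direction. The gain from using 24-month BMI does not depend on biased loss: at r = 0.7 the SD of the estimate falls by about 29% (1 − 0.714) even when loss is harmless.

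**What to change.** Make the primary analysis a model that uses 24-month BMI. The preferred choice is the mixed model already named, specified as follows: 24- and 36-month BMI for every randomised child, a common mean at baseline, the arm effect estimated at 36 months, and Study 1 group as covariate. Keep the observed-case regression and multiple imputation as sensitivity analyses. State the analysis set, and state that the primary model assumes data missing at random given the observed values.

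The cost is wording. The protocol names only a mixed model, so its terms must be written out, but no new data are needed and the sample size stays at 506 measured, around 600 randomised. The model does not protect against loss that depends on unobserved 36-month BMI beyond what 24-month BMI, arm and Study 1 group explain.

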### Assessor blinding

A CATI market survey company will be used to collect baseline at 2 years or outcome measures at 3 years through telephone interviews. Four RAs who are not involved in intervention implementation will conduct anthropometric measures via home visiting. The RAs and data entry staff will be blinded to treatment allocation. In addition, participating mothers will be blinded to the specific details of the research hypotheses and asked not to disclose treatment allocation.

### Cost-effectiveness analysis (CEA) and cost-utility analysis (CUA)

From a health provider perspective, the cost-effectiveness analysis will be conducted alongside the trial in which primary outcomes will be measured in natural units (e.g. BMI z-score). As supportive interventions for parents are likely to improve parent health-related quality of life, we will also do cost utility analysis. We will examine quality of life of the primary care-giver using the EuroQol 5 dimensions (EQ-5D) [27] at 1 year, 2 years and 3 years, which will allow calculation of quality adjusted life-years (QALYs).

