Based on the preliminary findings from the CHAT trial several advantages of using telephone support as a stand-alone program have been identified. Telephone support was seen by the mothers as more personal and increased the mother’s self-reported likelihood of identifying and addressing challenges with practising the desired health behaviours that influence healthy weight gain (detailed findings to be reported elsewhere). However, these advantages can be reduced by the time and effort spent contacting the participants. On average, the intervention nurse has needed to make 6–10 call attempts to each participant for one successful telephone support session, which is not an efficient use of resources (nurse time). On the other hand, using SMS has advantages as an efficient, simple and lower-cost method to deliver information to mothers and to respond quickly to their queries. Participants can also review responses at a time of their convenience. This is particularly useful for mothers with strong demands on their time. Despite the fact that the text messages were bi-directional, there was limited capacity for the intervention nurses to gather a detailed understanding of the challenges being experienced by mothers through SMS, and responses to mothers were likely to be brief. Thus, the combined intervention (Tel + SMS) being investigated in this new study seeks to mirror a real-life situation where interventions such as telephone support rarely occur in isolation and are often accompanied by SMS reminders and missed call messages. By combining telephone and SMS into an intervention delivery, we will be able to compensate for inherent limitations of each element and greatly improve their collective effectiveness.

Therefore, in this study protocol we are undertaking a new RCT which will be linked with the existing 3-arm RCT using the same study participants (see Fig. 1). This approach will enable us to use the 24-month survey for dual purposes in the existing 3-arm CHAT RCT (Study 1) and the new RCT (Study 2). For Study 1, the 24-month survey will measure the intervention outcome and effectiveness of either the telephone support intervention or the SMS intervention. For Study 2, the 24-month survey will be an integral part of the recruitment process and baseline data collection for this new RCT in determining the effectiveness of a combined telephone and SMS intervention.

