### Randomisation

After completing the 24-month (baseline) survey and measurement, participating mothers will be randomly allocated to either the intervention (Tel + SMS) or the control group (Control 2). Randomisation will take place using a web-based tool (http://www.randomization.com/). The intervention allocation scheme will be generated using random permuted blocks stratified by the group allocation in Study 1 (see Fig. 1). The use of stratified randomisation is to ensure that any carry-over effect of the CHAT intervention of Study 1 will be equally distributed between treatment groups in Study 2.

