### Analysis of costs

Data will be collected prospectively on the costs of delivering the intervention program (including telephone calls, SMS, the 2-way SMS service, staff time, training, mail outs, and any other intervention resources) from 2 to 3 years. These will only include the costs of all resources needed to reproduce the intervention. The cost of all intervention materials will be based on market prices. The reference year for the analysis will be 2019. All costs will be in Australian dollars and indexed to that year using the Health Price Index and all costs and effects will be appropriately discounted.

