### Outcomes for CEA

Similar to a previous evaluation of the Healthy Beginnings Trial [16], BMI and BMI z-score will be used to assess the cost-effectiveness of the intervention compared with the control group at 2 years (for Study 1) and at 3 years (Study 2). Incremental cost-effectiveness ratios will be calculated in terms of the incremental cost: a) per unit BMI reduction per child at 3 years, and 2) per QALY gained. Uncertainty in mean costs, outcomes and ICERs will be determined through bootstrapping. Scatter plots of the joint distribution of incremental costs and effects will be displayed on a cost-effectiveness plane and the probability of the intervention being cost-effectiveness will be determined for different willingness-to-pay thresholds.

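### The Study 2 QALY period is not tied to 24–36 months, and no adjustment for 24-month EQ-5D is stated, which leaves avoidable noise in the cost-utility result

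*Protocol article*

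**What the plan says.** All references are to the protocol article.

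- **Cost-effectiveness analysis (CEA) and cost-utility analysis (CUA):** the primary care-giver's EQ-5D is collected "at 1 year, 2 years and 3 years, which will allow calculation of quality adjusted life-years (QALYs". No interval is assigned to Study 1 or to Study 2.
- **Randomisation:** "After completing the 24-month (baseline) survey and measurement, participating mothers will be randomly allocated". The Background agrees: for Study 2, "the 24-month survey will be an integral part of the recruitment process and baseline data collection for this new RCT".
- **Background, on the other trial:** "For Study 1, the 24-month survey will measure the intervention outcome and effectiveness".
- **Analysis of costs:** delivery costs are counted for items that include "mail outs, and any other intervention resources) from 2 to 3 years".
- **Outcomes for CEA:** BMI and BMI z-score are used to assess cost-effectiveness "compared with the control group at 2 years (for Study 1) and at 3 years (Study 2". Ratios are then planned per unit of BMI at 3 years and per QALY. The QALY ratio has no stated period. On uncertainty: "Uncertainty in mean costs, outcomes and ICERs will be determined through bootstrapping".
- **Data analysis:** the primary Study 2 analysis adjusts for Study 1 treatment group, and secondary analyses add exact age. No baseline value of any outcome is named as a covariate.

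**The concern.** The listed times are read here as child ages, as elsewhere in the article. The 1-year EQ-5D is then taken a year before Study 2 randomisation, and neither it nor the 1-to-2-year interval can reflect the combined telephone and SMS intervention. The numerator of the Study 2 ratio has a fixed one-year window and the QALY denominator has none. Two analysts following the text could compute QALYs over different periods and report different ratios.

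Within the 2-to-3-year window only two EQ-5D values exist, so the 24-month baseline carries half the weight of the QALY. If arms are compared without regard to that baseline, a chance difference at 24 months passes into the incremental QALY. Bootstrapping describes this variation but does not remove it.

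Cost-effectiveness is among the main outcomes in the Abstract and among the hypotheses and research questions, and the Discussion expects the results to inform funding decisions. The precision of the incremental QALY therefore matters.

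**Working it through.** **Figures in the plan.** The article states no EQ-5D or QALY figure, so there is none to reproduce. The only number borrowed is 253 per arm at 3 years, from the Sample size section. It checks: 2 × (1.96 + 0.8416)² × (1.60/0.40)² = 251.2, so 252 per arm by the normal formula; the t-based value is 252.1, which rounds up to 253. For attrition, 506/0.85 = 595.3, so 596, or around 600.

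**Assumptions, not in the article.** EQ-5D standard deviation s between 0.10 and 0.20, equal at each time. Correlation r between any two times of 0.4 to 0.7, with 0.4 to 0.6 used for the headline figures. Complete data, and QALYs by the trapezoid rule.

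**Formulas per mother.**

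1. QALY over 1–3 years = 0.5·u12 + u24 + 0.5·u36. Variance = s²(1.5 + 2.5r).
2. QALY over 2–3 years = 0.5·u24 + 0.5·u36. Variance = s²(1 + r)/2.
3. QALY over 2–3 years adjusted for u24. Residual variance = s²(1 − r²)/4.
4. Ratio of (3) to (2) = (1 − r)/2. Both s and the sample size cancel.

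The standard error of the difference between arms is the square root of the variance × 2/253, and √(2/253) = 0.0889.

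**Results at s = 0.15.**

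| Quantity | r = 0.4 | r = 0.6 |
|---|---|---|
| SE, 1–3 years, unadjusted | 0.15 × √2.5 × 0.0889 = 0.0211 | 0.15 × √3.0 × 0.0889 = 0.0231 |
| SE, 2–3 years, unadjusted | 0.15 × √0.70 × 0.0889 = 0.0112 | 0.15 × √0.80 × 0.0889 = 0.0119 |
| SE, 2–3 years, adjusted | 0.15 × √0.21 × 0.0889 = 0.0061 | 0.15 × √0.16 × 0.0889 = 0.0053 |
| Variance ratio, adjusted to unadjusted | 0.6/2 = 0.30 | 0.4/2 = 0.20 |

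Adjustment therefore removes 70% to 80% of the variance, or 45% to 55% of the standard error (1 − √0.30 and 1 − √0.20).

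**Cost of the extra year.** The 1–3 year standard error is √(2.5/0.70) = 1.89 times the 2–3 year one at r = 0.4, and √(3.0/0.80) = 1.94 times at r = 0.6. The added year precedes randomisation and contains no Study 2 effect, so the increase is pure noise.

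**Chance imbalance.** The standard error of the 24-month difference is 0.15 × 0.0889 = 0.0133. A difference of d at 24 months enters the unadjusted QALY as d/2 directly and is expected to enter as a further r·d/2 through the 36-month value, (1 + r)/2 × d in all. One standard error of imbalance therefore carries 0.7 × 0.0133 = 0.0093 QALY at r = 0.4 and 0.8 × 0.0133 = 0.0107 at r = 0.6. Averaged over randomisations the contribution is zero.

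**Across s = 0.10 to 0.20 and r = 0.4 to 0.7.** Standard errors are 0.014–0.032 (1–3 years), 0.007–0.016 (2–3 years, unadjusted) and 0.003–0.008 (2–3 years, adjusted). One standard error of imbalance carries 0.006–0.015 QALY.

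**The case against.** The strongest case on the other side has four parts.

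- **The period can be inferred.** The economic section covers both trials, and the 24-month survey serves both. A natural reading is 1 to 2 years for Study 1 and 2 to 3 years for Study 2, in line with the cost window. A reader might infer that the plan builds Study 2 QALYs over all three times; the document does not say so. It does not rule it out either. The sentence that separates the studies concerns BMI and BMI z-score, the QALY ratio has no stated window, and the costs described begin at 2 years, after the Study 1 intervention ends, so they could not support a Study 1 ratio. The intended discounting of effects also sits oddly with a single-year horizon. The ambiguity stands.
- **No adjustment is silence, not a choice.** A reader might take the bootstrap of mean outcomes to mean unadjusted means. The text does not say that, and a bootstrap is fully compatible with regression in each sample. This objection stands: the plan cannot be said to have chosen an unadjusted analysis.
- **There is no bias.** Randomisation follows the 24-month survey, so baseline utility is balanced in expectation. A reader might infer a systematically distorted ratio; that is not supported. A correct bootstrap interval already reflects the sampling variation. What remains is that this interval would be wider than it need be.
- **Covariates are commonly left to a health-economic plan.** This is a condensed article and no such plan is shown, so the missing covariate is not an error. The baseline adjustment is put forward as an improvement, not as a correction of something stated wrongly.

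**Conclusion.** The point holds as a wording gap with a worthwhile improvement attached. The article lists three EQ-5D times as the basis for QALYs and does not tie an interval to Study 2, although randomisation and the cost window both place Study 2 between 24 and 36 months. That permits a pre-randomisation year to enter, which would roughly double the standard error of the incremental QALY (1.9 to 2.0 times for correlations of 0.4 to 0.7). No adjustment for 24-month utility is stated. An unadjusted comparison would be valid on average but imprecise: adjustment would cut the variance by about 70% to 80% at correlations of 0.4 to 0.6.

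That percentage does not depend on the EQ-5D standard deviation or the sample size, but it does depend on the assumed correlation and on equal spread at the two times. The absolute QALY figures rest on an assumed standard deviation as well. No figure stated in the article changes, and the BMI primary outcome is unaffected.

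**What to change.** Make three changes to the economic sections, or to the health-economic analysis plan if there is one:

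1. State that Study 2 QALYs cover 24 to 36 months, from the 24- and 36-month EQ-5D, matching the cost window.
2. Assign the 1-year EQ-5D to Study 1.
3. Estimate incremental QALYs by regression on arm, Study 1 group and 24-month utility, refitted within each bootstrap sample, with each mother's costs and utilities resampled together so that their joint distribution is kept.

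The cost is a few sentences and a small change to the analysis code. The 24-month EQ-5D is already scheduled, so no visit, questionnaire or change in sample size is needed.
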